### Imputation procedure for missing data

We will report the reasons for withdrawal for the different randomization groups and will compare the reasons qualitatively. The effect that any missing data might have on the results will be assessed via sensitivity analysis of augmented data sets. Dropouts (essentially participants who withdraw consent for continued follow-up) will be included in the analysis using modern imputation methods for missing data.

### Quality assurance

To ensure that treatments are of a high standard and delivered in accordance with the trial protocol, all acupuncturists will have a TCM certificate and at least 1 year of experience, will take a study-specific theoretical course, and will undergo study-specific practical training. Three training sessions lasting 1–3 days each will take place before the beginning of the study, and then a single 4-h training session will be given 1 month after the beginning of the study. The acupuncturists are graduate students in TCM and have received general acupuncture training during their studies. All acupuncturists have to pass the theoretical and practical tests.

### Study governance and management

The study will be led by a steering committee consisting of an independently selected chair, site PIs, and other investigators. Each of these individuals will have one vote, and decisions will be reached by majority consensus and a formal vote. The steering committee will meet face to face four times per year and monthly via phone conferences and will communicate through email on a regular basis. Additionally, the study will have subcommittees, including a protocol committee, a recruitment committee, and a publication committee.

The independent DSMB will hold regular conference calls to review the protocol with respect to ethical and safety standards, to monitor the safety of the trials, to monitor the integrity of the data with respect to the original study design, and to provide advice on study conduct. The DSMB will also have the power to terminate the study for a variety of reasons, including poor recruitment, AEs caused by the study medications, or a clear trend in live births in one of the blinded treatment arms exceeding our expectations.

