#### Adverse events

All AEs will be categorized, and the percentage of patients experiencing AEs and serious adverse events (SAEs) during the treatment period and follow-up period will be documented and reported. For fetuses, SAEs and AEs will be reported as those occurring after 20 weeks of gestation through birth, and for newborns, SAEs and AEs will be reported as those occurring within 28 days after birth. SAEs will include events that are fatal or immediately life-threatening, severely or permanently disabling, or that require hospitalization; overdoses (intentional or accidental); congenital anomalies; pregnancy loss after 12 weeks of gestation; neonatal death up to 6 weeks after delivery; or any event deemed to be serious by the site PIs. The Data and Safety Monitoring Board (DSMB) will review AEs on a quarterly basis and will review SAEs immediately.

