### Sample size calculations

In previous studies, the overall live birth rate for infertile women with PCOS who received letrozole for 6 months was 36.3% [28], whereas for women who received fixed acupuncture twice per week with a maximum of 32 acupuncture treatments, the overall live birth rate was 13.9% [10]. Thus, we hypothesize that the live birth rate is 35% for four cycles of letrozole treatments and 15% for fixed acupuncture three times per week. We have chosen 10% as the minimal clinically detectable difference that is likely to change clinical practice. Assuming a 35% live birth rate with letrozole, a 25% live birth rate with personalized acupuncture, a 15% live birth rate with fixed acupuncture, a 5% live birth rate with placebo letrozole, and an 80% power at a significance level of 0.05, we calculated that 250 subjects per treatment group were required. The sample size was increased from 250 to 275 per group considering a 10% dropout rate, and thus 1100 women in total will be enrolled.

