### Data analysis

The primary analysis will use an intention-to-treat approach to examine differences in the live birth rate among the four treatment groups. Primary efficacy analysis will be performed by comparing the treatment groups with respect to the primary outcome of live birth using the Pearson chi-square test. For the secondary supportive analysis, we will fit a logistic regression model to compare the treatment arms with respect to the primary outcome of live birth, adjusting for other factors such as randomization stratification of study site and prior exposure to study medications. Comparisons of variables such as live birth rate, ovulation rate, conception rate, pregnancy rate, multiple pregnancy rate, and miscarriage rate will include relative risk and 95% confidence intervals in addition to the chi-square test. Changes in laboratory values will be assessed by analysis of covariance (ANCOVA).

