The analysis of secondary (supplemental) outcomes measured over time will entail the application of statistical methods that have been developed for correlated data because repeated observations will be made over time for each individual. For secondary outcomes such as hormone levels, a linear mixed-effect model will be fit where the main independent variables will be treatment group, time, and their interaction as well as the designed randomization stratification factors as covariates. Logistic regression models will be used in secondary analyses to evaluate the predictive value of treatment arm, clinical site, body mass index, and other explanatory variables on binary outcomes (e.g., live birth, abortion). Cox proportional hazards models and the Kaplan-Meier method will be used to compare time to pregnancy in the treatment groups. Effects on QOL, as determined by the change from baseline physical and mental component scores, will be analyzed by univariate and multivariate ANCOVA. The adequacy of blinding will be tested by Fisher’s exact test comparing true group assignments with participant guesses, including “don’t know.” In order to evaluate acupuncture as a unique therapy, the combination of the personalized acupuncture group and fixed acupuncture group will also be compared with the combination of the letrozole and placebo letrozole groups for the analysis of primary outcome. Differences in AE rates will be analyzed in a negative binomial generalized linear model. A *P* value < 0.05 with a two-tailed test will be considered significant. All statistical analyses will be performed using IBM SPSS Statistics version 21.0 software (IBM Corp., Armonk, NY, USA).

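### The DSMB's stated efficacy ground judges one arm's live births against a planning guess, not against another arm, and neither the sample size nor the final 0.05 test allows for such a stop

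*Protocol article*

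**What the plan says.** Under Study governance and management, the protocol article states: "The DSMB will also have the power to terminate the study for a variety of reasons". Besides poor recruitment and adverse events caused by the study medications, the reasons listed include "a clear trend in live births in one of the blinded treatment arms exceeding our expectations".

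The only expectations in the article are in Sample size calculations: "Assuming a 35% live birth rate with letrozole, a 25% live birth rate with personalized acupuncture", "a 15% live birth rate with fixed acupuncture" and 5% with placebo letrozole. They lead to 250 women per arm at 80% power, raised to 275 for dropout.

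The Objectives set out three live-birth hypotheses, each comparing one arm with the next: letrozole over personalized acupuncture, personalized over fixed, and fixed over placebo. Data analysis does the primary analysis by "comparing the treatment groups with respect to the primary outcome of live birth using the Pearson chi-square test", and a *P* "value < 0.05 with a two-tailed test will be considered significant". The article mentions no adjustment for early looks at live birth. The only review frequency it gives is for safety: the DSMB "will review AEs on a quarterly basis and will review SAEs immediately".

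**The concern.** The clause does more than leave out detail. It states an efficacy ground for ending the whole four-arm trial, and that ground does not measure a treatment effect. An arm can exceed its planning rate because the recruited women are more fertile than assumed, in which case every arm may be high with no difference between them.

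The planning rates are also soft. The 35% is drawn from 36.3% in a study of 6 months of letrozole, while this trial gives four cycles. The 15% is drawn from 13.9% with acupuncture twice weekly, while this trial gives it three times weekly. No source is cited for the 5%. The clause also speaks of blinded arms. If the labels are masked from the DSMB, it cannot tell which of the four rates an arm should be held against.

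A stop on this ground selects an arm at a high point, so that arm's rate is overstated. It also ends comparisons that need the full sample, and the data are then tested at an unadjusted 0.05.

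**Working it through.** **1. The plan's own figure.** For two proportions with pooled variance under the null, two-sided 0.05 and 80% power:

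n = [1.960·√(2p̄(1−p̄)) + 0.8416·√(p₁(1−p₁)+p₂(1−p₂))]² / (p₁−p₂)².

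For 25% v 15%: (1.960×0.5657 + 0.8416×0.5612)² / 0.01 = 1.581² / 0.01 = 250, an exact match. The other adjacent pairs give 329 (35% v 25%) and 141 (15% v 5%). The 275 is 250×1.10. The figure therefore contains no allowance for interim looks.

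**2. False signal at one look, all four planned rates true.** Exact binomial tails, with independent arms. For an excess of more than 5 points at 100 per arm:

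- P(X>40 | 0.35) = 0.125
- P(X>30 | 0.25) = 0.104
- P(X>20 | 0.15) = 0.066
- P(X>10 | 0.05) = 0.0115

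P(any arm) = 1 − 0.875×0.896×0.934×0.9885 = 0.276. The same sum at 125 per arm gives 0.241. For more than 10 points it is 0.027 at 100 and 0.018 at 125. For more than 1.96 SE at 125 it is 0.103. For any excess at all at 125 it is 0.93.

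**3. False signal over repeated looks.** Simulation with the planned rates true and assumed looks at 50, 100, 150, 200 and 250 per arm:

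| Reading of a clear excess | P(any arm, any look) |
|---|---|
| 3 SE | 3% |
| 10 points | 16% |
| 1.96 SE | 28% |
| 5 points | 54% |

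The look at 250 is the planned final sample, so it is not an early stop. Without it the 5-point figure is still 54%. The look at 50 supplies 42 of those 54 points. There, 5 points is only 0.05/√(0.35×0.65/50) = 0.05/0.0675 = 0.74 SE for the 35% arm.

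**4. Type I error if the signal stops the trial and the test stays at 0.05.** Simulation at 250 per arm with 1, 3 or 11 interim looks (assumed) and 5-point or SE thresholds:

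| Setting | 1 look | 3 looks | 11 looks |
|---|---|---|---|
| All arms 15%, expectation 15%: one pair | 0.058 | 0.062–0.064 | 0.065–0.079 |
| Same: four-arm test | 0.062–0.064 | 0.070–0.075 | 0.060–0.097 |
| Letrozole = personalized = 25%, others as planned: that pair | 0.054–0.057 | 0.058–0.060 | 0.067–0.070 |

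Where fixed and placebo are both 5%, the pair's error with 11 looks is 0.033–0.059, so inflation is not universal. If any excess at all stops the trial, the error stays near 0.05, but almost every trial then ends early.

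**5. What an early stop costs.** Take a stop at 125 per arm for 25% v 15%. Power = Φ[(0.10 − 1.960·√(2×0.20×0.80/125)) / √((0.1875+0.1275)/125)] = Φ[(0.10 − 0.0992)/0.0502] = Φ(0.02) = 51%, against the planned 80%. At 100 per arm, a 35% arm that passes the 5-point mark shows at least 41 births in 100.

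**The case against.** The clause grants a discretionary power. It does not oblige the DSMB to stop, and the word clear excludes trivial excesses. A reader might infer a mechanical rule that fires about half the time. The text does not support that: the 54% needs a 5-point threshold and a look at 50 per arm, both assumptions, and stricter readings give 2–3%. Under masked labels another reading is possible, namely an arm above anything expected. P(any arm above 40%) at 100 per arm is then about 12.5%, which is inside the range shown.

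A reader might also infer a large type I inflation. One comparison tested at an unadjusted 0.05 at every look does reach 0.083 with one interim look, 0.124 with three and 0.210 with eleven. The protocol does not describe such testing, and the quarterly review concerns adverse events, not live births. Those figures belong to a different rule.

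Finally, boundaries and look times may sit in a DSMB charter or analysis plan that is not shown, so their absence here is not a fault. All of this limits the size of the point. It does not rescue the stated ground: a charter with a sound between-arm boundary would contradict this clause, and the clause would still need correcting.

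**Conclusion.** The point holds in a limited form. The article names an efficacy ground based on one arm against an assumed rate, in a trial whose hypotheses and primary test are between-arm, whose size is a fixed-design figure and whose final test uses the full 0.05.

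How easily chance could produce such a signal depends on thresholds and looks that the article does not define. It runs from about 2–3% to 24–28% at one look at 100–125 per arm, and from 3% to 54% over five looks. The type I error is not protected, but the inflation is moderate: about 0.054–0.08 for a pair in most settings tried, up to about 0.10 for the four-arm test, and near 0.05 if any excess counts. The main harm is a stop on a random high or a wrong planning rate, leaving an overstated arm and underpowered comparisons. The clause should be changed.

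**What to change.** Delete the single-arm ground and keep the safety and recruitment grounds as they are. Then choose one of two options.

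- **No efficacy stopping.** This matches the fixed-design sample size and the 0.05 as written.
- **Efficacy stopping on the adjacent comparisons only.** These are letrozole v personalized, personalized v fixed, and fixed v placebo. Use a Haybittle-Peto boundary (two-sided p<0.001) at looks fixed in advance, for example when one third and two thirds of live-birth outcomes are known. State that letrozole v placebo, or any other non-adjacent contrast alone, is not a ground, and that one crossing does not end the comparisons still open.

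The restriction to adjacent pairs is essential. Under the planned rates at one third (83 per arm), letrozole v placebo alone crosses p<0.001 with probability 97% and at least one of the six pairs with 98%, whereas at least one adjacent pair crosses in only 17%. A boundary on any pair would end nearly every trial before the stated hypotheses could be answered.

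With two interim looks at p<0.001, the error of one comparison stays at about 0.050 with the final test at 0.05, so the sample size need not change. This figure is per comparison and does not settle multiplicity across the three. The cost is one paragraph in the protocol and matching text in the DSMB charter. The small downside is that early stopping for benefit becomes harder.

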### Data access, management, and quality control

Both the case report form (CRF) and a web-based electronic database will be used to manage individual participant data. Quality control of the data will be handled at three different levels. First, the investigators will be required to ensure the accuracy of the data when they input the data from the CRF. The second level will include data monitoring and validation that will be carried out by the DCC staff. The third level will be the site visits, during which the data in ResMan will be compared with the source documents. Identified errors will be resolved by ResMan and the clinical sites.

The ResMan database will be used as a double-input database. The ResMan staff will oversee the intrastudy data-sharing process. All PIs will be given access to the cleaned data sets. Project data sets will be housed on the ResMan database system for the duration of the study, and all data sets will be password-protected. The PIs will have direct access to their own site’s data sets as well as access to other sites’ data by request. To ensure confidentiality, data dispersed to project team members will be blinded to any identifying participant information.

### Ethics and dissemination

All women and their husbands will be asked to sign a consent form prior to joining the study, and they will be made fully aware that they are free to withdraw from the study at any time. The results of this trial will be disseminated in peer-reviewed journals and presented at international meetings.

## Discussion

To the best of our knowledge, no previous study has investigated whether personalized acupuncture has the potential to increase the live birth rate in infertile women with PCOS. Our study is thus the first multicenter randomized controlled trial to compare the effects of personalized or fixed acupuncture with letrozole or placebo letrozole on live birth in infertile women with PCOS. The hypothesis is that letrozole is more effective than personalized acupuncture, that personalized acupuncture is more effective than fixed acupuncture, and that fixed acupuncture is more effective than placebo letrozole. Moreover, we hypothesize that personalized acupuncture is more likely than letrozole to reduce miscarriage rate and the risk of pregnancy complications.

Considering the treatment principle based on syndrome/pattern differentiation in TCM, the kidney, liver, and spleen are the top three zang-fu organs associated with the development of PCOS, and yin or yang deficiency is the essential cause, whereas pathological products such as phlegm are superficial [29]. Therefore, the therapeutic proposal should reinforce liver-kidney-yin deficiency, promote spleen-kidney-yang circulation, and resolve phlegm. We will divide the individual groups into two types according the theory of TCM as “liver-yin and kidney-yin deficiency” and “spleen-yang and kidney-yang deficiency.” This method is similar to that of actual clinical practice and can be used in future studies. The fixed acupuncture regimen is controversial based on the TCM theory of acupuncture.

## Trial status

This trial was approved on March 9, 2018. The recruitment began on August 13, 2018, and is expected to be completed by August 13, 2021. The trial procedures are expected to be completed by the end of May 2022, when considering 10-month pregnancies and the follow-up time for collecting information regarding live births. This is version 3.0 of the protocol, dated May 12, 2019.

## Data Availability

The supplementary data, except for private information, will be stored on a public website (e.g., Dryad, https://datadryad.org/stash).

## Abbreviations

AE: Adverse event
ALT: Alanine aminotransferase
ANCOVA: Analysis of covariance
AST: Aspartate aminotransferase
BUN: Blood urea nitrogen
ChQOL: Chinese Quality of Life instrument
CONSORT: Consolidated Standards of Reporting Trials
CRF: Case report form
CV: Conception vessel
DCC: Data coordinating center
DSMB: Data and safety monitoring board
E2: Estradiol
EX-CA: Extra point of chest and abdomen
FG: Ferriman-Gallwey
FSH: Follicle-stimulating hormone
GV: Governor vessel
HbA1c: Glycated hemoglobin
HCG: Human chorionic gonadotropin
HDL-C: High-density lipoprotein cholesterol
HPV: Human papillomavirus
K: Kidney
LDL-C: Low-density lipoprotein cholesterol
LH: Luteinizing hormone
LI: Large intestine
LR: Liver
P: Progesterone
PC: Pericardium meridian
PCOS: Polycystic ovary syndrome
PCOS-QOL: Polycystic Ovary Syndrome Quality of Life Questionnaire
PI: Principal investigator
PRL: Prolactin
PSQI: Pittsburgh Sleep Quality Index
QOL: Quality of life
RCT: Randomized controlled trial
ResMan: Research Management
SAE: Serious adverse event
SAS: Zung Self-Rating Anxiety Scale
SDS: Zung Self-Rating Depression Scale
SF-36: 36-Item Short Form Health Survey
SHBG: Sex hormone–binding globulin
SP: Spleen
SPIRIT: Standard Protocol Items: Recommendations for Interventional Trials
ST: Stomach
STRICTA: Standards for Reporting Interventions in Clinical Trials of Acupuncture
T: Testosterone
TCM: Traditional Chinese medicine
TCT: ThinPrep cytologic test
TORCH: Toxoplasma, rubella virus, cytomegalovirus, herpesvirus
TSH: Thyroid-stimulating hormone
